### Sample size

The sample size calculations were performed based on formulae provided by Cohen [32] and based on the following parameters: (1) *α* = 0.05, 2-sided; (2) *β* = 0.20, power = 80%; and (3) our previous study reported that suprapatellar pouch effusion maximum area in older people with knee pain was 2.0 ± 1.5 cm^2^. To determine an expected rate of effusion-synovitis decrease after MTX treatment of 35% [33], the calculated sample size will be 74 per arm (Table 2). A study from our group reported that patients with knee OA had a VAS knee pain score (0–100) of 50 ± 20 [26]. Assuming knee pain in OA patients will be reduced by 20% following MTX treatment, the sample size needed to detect these differences is 64 per group (Table 2). A decrease in knee pain of 20% or more is deemed clinically relevant [34]. Therefore, 100 patients in each arm (allowing for a 20% dropout over 52 weeks) will be sufficient to detect the differences between the treatment and placebo groups. The participants will be recruited from 9 study sites, and competitive recruitment strategy will be implemented.

**Table 2 Tab2:** Sample size calculation

	Mean (SD)	Detectable difference	Calculated sample size (per arm)
Suprapatellar pouch effusion (cm^2^)	2.0 ± 1.5	35%	74
VAS knee pain (0–100)	50 ± 20	20%	64

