### Statistical analysis plan

Intention-to-treat and per-protocol (for patients who have taken > 80% the study medication) analyses of primary and secondary outcomes will be performed. The changes in outcome measures among all randomised participants at 52 weeks will be used for intention-to-treat analyses. Independent *t* tests and chi-square tests will be used to examine baseline characteristics of participants between groups. General linear mixed models to account for the effects of clustering by trial sites will be used to compare changes in outcomes in univariable and multivariable modelling between groups. Additional adjustment for imbalanced baseline factors will be made for further analyses. Baseline data will be used for data imputation assuming missing at random. A 95% confidence interval not including the null point or a *p*-value < 0.05 (two-tailed) will be considered statistically significant.

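### The plan compares 52-week changes without prespecifying the baseline outcome value as a covariate or naming a primary model, and picks extra covariates by observed imbalance; a baseline-adjusted primary model would gain precision at no cost

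*Protocol article*

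**What the plan says.** All of this is in the Protocol article.

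- **Outcome and model (Statistical analysis plan).** The intention-to-treat analysis uses changes at 52 weeks. Linear mixed models that allow for clustering by site "will be used to compare changes in outcomes in univariable and multivariable modelling between groups". The covariates of the multivariable model are not listed, the baseline value of the outcome is not mentioned as a covariate, and neither model is called primary.
- **Baseline comparison (same section).** Independent t tests and chi-square tests "will be used to examine baseline characteristics of participants between groups".
- **Further covariates (same section).** "Additional adjustment for imbalanced baseline factors will be made for further analyses". The article does not define imbalance.
- **Sample size.** The effusion calculation rests on an earlier study in which "suprapatellar pouch effusion maximum area in older people with knee pain was 2.0 ± 1.5 cm^2", with "an expected rate of effusion-synovitis decrease after MTX treatment of 35" percent. For pain, an earlier study found that "patients with knee OA had a VAS knee pain score (0–100) of 50 ± 20", and the calculation continues: "Assuming knee pain in OA patients will be reduced by 20% following MTX treatment". The results are 74 and 64 per arm, raised to "100 patients in each arm (allowing for a 20% dropout over 52 weeks".
- **Baseline data (Table 1).** VAS pain and the MRI effusion measure are both taken at screening.

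**The concern.** Two choices in the text are weaker than they need to be.

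First, a change score subtracts the whole baseline value whatever its correlation with the follow-up value. Unless that correlation is close to 1, this leaves noise that including the baseline value as a covariate would remove.

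Second, after proper randomisation any baseline difference between arms is chance. A covariate earns its place by predicting the outcome, not by happening to differ between arms. A rule that waits to see which factors differ lets the data settle the adjusted model. With at least two models planned and none named primary, the reader cannot tell in advance which result decides the trial.

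At stake are the precision of both primary comparisons and, if the correlation over a year is low, the stated 80% power. How the result is chosen is also left open.

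**Working it through.** **1. Reproduce the stated sample sizes.** Inputs from Sample size: two-sided alpha 0.05, power 80%.
- Effusion: difference 0.35 × 2.0 = 0.70 cm², SD 1.5, standardised difference 0.70/1.5 = 0.467. The exact two-sample t calculation gives 74 per arm.
- VAS: difference 0.20 × 50 = 10 points, SD 20, standardised difference 0.50. The exact calculation gives 64 per arm.

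Both match Table 2. With 100 per arm and 20% dropout, 80 per arm complete.

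**2. What those SDs mean for a change score.** 1.5 and 20 are SDs at one time point. With equal SDs at baseline and week 52 and correlation r:
- SD of change = SD × √(2(1 − r))
- residual SD after adjusting for baseline = SD × √(1 − r²)
- variance ratio, adjusted to change = (1 + r)/2

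The SD of change equals the cross-sectional SD only at r = 0.5. The article gives no r, so a range is shown.

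**3. Power at 80 completers per arm** (t test, two-sided 0.05, site effects ignored):

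| r | Effusion SD, change / adjusted | Effusion power | VAS SD, change / adjusted | VAS power | Variance saved |
|---|---|---|---|---|---|
| 0.3 | 1.775 / 1.431 | 70% vs 87% | 23.7 / 19.1 | 76% vs 91% | 35% |
| 0.5 | 1.500 / 1.299 | 83% vs 92% | 20.0 / 17.3 | 88% vs 95% | 25% |
| 0.7 | 1.162 / 1.071 | 97% vs 98% | 15.5 / 14.3 | 98% vs 99% | 15% |

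The unadjusted change analysis reaches 80% at r of about 0.45 for effusion and 0.37 for VAS. The adjusted analysis stays above 80% at every r examined (0 to 0.8).

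**4. Allow for the entry threshold on VAS.** Inclusion requires VAS of at least 40 mm. As an illustration, assume that 50 ± 20 describes unselected, normally distributed patients, that week 52 is linear in baseline, and that r is the correlation before selection. Cutting at 40 lowers the baseline variance from 400 to about 194.5 (SD about 13.9). The variance of change is then 400(1 − r²) + (1 − r)² × 194.5.
- r = 0.3: 364 + 95.3 = 459.3, SD 21.4; power 83% vs 91% adjusted.
- r = 0.5: 300 + 48.6 = 348.6, SD 18.7; power 92% vs 95%; variance saved 48.6/348.6 = 14%.

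The effusion grade threshold may act in the same way, but the article does not link grade to area, so this cannot be computed.

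**5. The data-dependent part.**
- With k independent baseline tests at 0.05, the chance that at least one flags an imbalance is 1 − 0.95^k: 40%, 54% and 64% for k = 10, 15 and 20. The number of tests is an assumption.
- A simulation under no treatment effect (80 per arm, r of 0.3, 0.5 and 0.7, 4,000 runs each) gave type I error of 4.6% to 5.8% for each fixed model.
- Adjusting for baseline only when its own test was significant gave 4.3% to 4.9%.
- Reporting the better of the unadjusted and baseline-adjusted results gave 6.5% to 8.2%.

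The inflation therefore comes from an open choice between models, not from the imbalance rule alone.

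**The case against.** The strongest reply is that the article condenses a fuller plan. Multivariable modelling is planned whatever the baseline tests show, and its unlisted covariates may include the baseline value. A separate analysis plan may also name the primary model. This stands as far as it goes: an unlisted covariate set is not in itself an error. It does not cover what the article does state, namely significance tests of baseline characteristics between randomised arms and adjustment for factors found imbalanced.

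A reader might infer that the main model leaves out baseline and that covariates enter only when a baseline test is significant. The text does not say so. Omission of baseline is certain only for the univariable model, the imbalance adjustment is additional and confined to further analyses, and no sentence makes the tests its trigger.

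A reader might also infer that the entry thresholds bias a change-score comparison through regression to the mean. They do not. Both randomised arms are selected in the same way, so the effect falls on both alike and the difference in change stays unbiased. Only precision is lost.

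Finally, the power shortfall is hypothetical. The design has 80 completers against 74 and 64 required, so r slightly below 0.5 is absorbed. At r = 0.7 the gain is about one percentage point, and on the illustration in step 4 the VAS shortfall at r = 0.3 disappears.

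**Conclusion.** The point holds as a free improvement to a stated method. The plan does not prespecify the baseline value as a covariate, does not name a primary model, and selects additional covariates by observed imbalance.

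Under equal SDs, prespecified baseline adjustment saves 15% to 35% of the variance for r between 0.7 and 0.3. At r = 0.5 that is worth a third more patients (1/0.75 = 1.33), but less for VAS if the 40 mm threshold narrows the baseline spread.

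The documents do not support calling the trial underpowered or the sample size wrong: 74 and 64 reproduce, and power falls below 80% only under the values of r given above. Nor do they show that type I error is inflated; that would require choosing the better of two results after seeing both.

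The figures rest on an assumed r and on a simple two-group comparison without site effects. The effusion figures also use the maximum area from the sample size section, whereas Outcome measures names volume as the endpoint, so they carry over only if the standardised difference is similar.

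**What to change.** For each continuous outcome, name one primary mixed model: week-52 value or change on treatment, site and the baseline value of that outcome. With baseline in the model, both forms of the outcome give the same treatment effect. List any further covariates now, chosen for expected prognostic value. Delete the adjustment for observed imbalance and the baseline significance tests, and keep a descriptive baseline table by arm. If a separate analysis plan already names such a model, confirm that it is primary and remove the conflicting sentence.

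The cost is a short text change, made before unblinding. The baseline values are already collected at screening, so no new data, visits or patients are needed.

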### Participants

At screening, participants will complete questionnaires, clinical examinations, blood tests (blood cell counts, liver function, renal function, hepatitis B/C tests), and chest X-ray and have a knee X-ray and MRI to ensure the inclusion/exclusion criteria are met. The index knee will be defined as the one with symptomatic OA; if both are symptomatic, the one with more severe knee symptoms will be used as the index knee. There will be 7 study visits (screening, baseline, and weeks 4, 12, 24, 36, and 52) (Fig. 1). The study measures are shown in Table 1. If the participant withdraws after a minimum of 24 weeks’ treatment, he/she will be requested to have a second knee MRI scan.

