### Withdrawal

All participants are able to withdraw at any time of the trial. The time and reason will be recorded. If participants withdraw after 6 months of follow-up, we will attempt to obtain their final MRI scans and pain levels.

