In vitro, MTX inhibited the production of cytokines induced by T cell activation, including IL-6, IL-13, interferon (IFN)-γ, and TNF-α [45]. Oral intake of 10 mg MTX by RA patients led to marked inhibition of cytokine production in blood drawn after 2 h [45]. MTX treatment (up to 15 mg for 24 weeks [46] or mean 8.7 mg for 1 year [15]) resulted in significant reductions of circulating IL-6, sIL-2R, and/or CRP. MTX (15 mg/week for 1 year) for the treatment of early RA significantly decreased disease activity as well as serum CRP and ESR levels [47]. In patients with RA, treatment with MTX reduced area of knee synovitis at the suprapatellar pouch by 35% [33]; inhibited inflammatory response in synovial tissue, including reducing numbers of macrophage, and suppressing expressions of intercellular adhesion molecule 1, IL-1, TNF-α, and CRP [48]; and decreased BMLs and synovitis even at very early stage [49].

Therefore, we propose MTX for the treatment of mid- to late-stage knee OA with the aim to reduce local and systemic inflammatory cytokines, to control patients’ joint inflammation, to alleviate knee pain, and to delay the time of joint replacement. In view of the side effect of MTX and the study population which are mainly older adults, we will give folic acid tablets to reduce the side effects and pay close attention to the patients who cannot tolerate MTX. In previous studies, MTX was used at dosages of 20–25 mg/week for 6 months to test if it was effective to reduce symptoms and disease progression in knee OA patients [19]. In our study, we will choose the highest dosage of 15 mg/week and the total course of 52 weeks, with consideration of the ethnic differences and slow-acting property of this drug. MTX is a slow-acting drug, and the onset time is generally 3 to 6 months. We will assess the pain 6 times during the trial and measure MRI changes at baseline and 52 weeks. One year will be enough to observe the treatment effect on effusion-synovitis and Hoffa’s synovitis. In the future, joint replacement surgery and cartilage loss as the final OA outcomes could be recorded.

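### Missing week-52 outcomes are imputed from baseline data under missing at random: carried forward, this is not an MAR method; used as predictors, it leaves out four pain visits

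*Protocol article*

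**What the plan says.** The Statistical analysis plan section sets the intention-to-treat outcome: "The changes in outcome measures among all randomised participants at 52 weeks will be used for intention-to-treat analyses". On missing values it has one sentence: "Baseline data will be used for data imputation assuming missing at random". The model is described by its handling of sites: "General linear mixed models to account for the effects of clustering by trial sites will be used to compare changes in outcomes". No repeated-measures use of the visits is stated.

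The data available are wider than baseline. Under Participants: "There will be 7 study visits (screening, baseline, and weeks 4, 12, 24, 36, and 52"). Table 1 schedules VAS and WOMAC at screening, at each visit from week 4 to week 52, and at withdrawal. The Discussion confirms this: "We will assess the pain 6 times during the trial and measure MRI changes at baseline and 52 weeks". For those who leave, the Withdrawal section adds: "If participants withdraw after 6 months of follow-up, we will attempt to obtain their final MRI scans and pain levels". The Sample size section sets 100 per arm, "allowing for a 20% dropout over 52 weeks".

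**The concern.** The rule decides what every participant without a week-52 value contributes to both co-primary results, and the trial is sized for up to a fifth of participants to be in that position.

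Carrying baseline forward is a fixed assumption that leavers do not change at all. It conflicts with the MAR assumption in the same sentence, and it treats assigned zeros as observed data. Using baseline variables as predictors is consistent with MAR only if, within arm, dropout depends on nothing observed after baseline. The trial records pain four times between baseline and week 52, and those values are natural predictors of both leaving and final pain. At stake are the size of the estimate, the type I error when dropout differs between arms, and an analyst's choice between two readings that can give different primary results.

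**Working it through.** **1. The plan's own figures.** n per arm = 2(1.96 + 0.8416)² (SD/δ)², where 2(1.96 + 0.8416)² = 15.70.
- MRI: the plan's input is "suprapatellar pouch effusion maximum area in older people with knee pain was 2.0 ± 1.5 cm^2", so δ = 0.35 × 2.0 = 0.70. 15.70 × (1.5/0.70)² = 72.1; the t-test version is 73.05, so 74.
- VAS: δ = 0.20 × 50 = 10, SD 20. 15.70 × 4 = 62.8; the t-test version is 63.77, so 64.
- Dropout: 74/0.8 = 92.5 (93) and 64/0.8 = 80, so 100 per arm covers 20%.

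The stated sample sizes reproduce. With 80 completers per arm, power is 0.885 (VAS) and 0.839 (MRI).

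**2. Reading A, baseline carried forward.** In an arm with dropout p, true mean change μ and SD of change s:
- mean after imputation = (1 − p)μ
- variance after imputation = (1 − p)s² + p(1 − p)μ²

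With p = 0.20 in both arms, the VAS difference is 0.8 × 10 = 8 mm and the MRI difference 0.8 × 0.70 = 0.56 cm².

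For VAS I take s = 20 (the plan's SD, assumed to apply to change), 100 per arm and a normal approximation. The unequal splits and the placebo improvements are assumptions; the documents give neither.

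| Dropout MTX/placebo | True improvement MTX/placebo (mm) | Difference after imputation (mm, positive favours MTX) | SE | Rejection rate |
|---|---|---|---|---|
| 20/20% | 10/0 | 8.0 | 2.56 | 0.88 |
| 20/20% | 20/10 | 8.0 | 2.68 | 0.85 |
| 30/10% | 10/0 | 7.0 | 2.57 | 0.78 |
| 30/10% | 20/10 | 5.0 | 2.71 | 0.45 |
| 10/30% | 20/10 | 11.0 | 2.64 | 0.99 |
| 30/10% | 10/10 | −2.0 | 2.59 | 0.12 |
| 25/15% | 10/10 | −1.0 | 2.59 | 0.07 |
| 30/10% | 0/0 | 0.0 | 2.53 | 0.05 |

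Example, sixth row: means −7 and −9; variances 0.7 × 400 + 0.21 × 100 = 301 and 0.9 × 400 + 0.09 × 100 = 369; SE = √(670/100) = 2.59; 2/2.59 = 0.77; two-sided rejection about 0.12. Simulation with 20,000 replicates gave 0.119 for this row and 0.837 for the second.

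For MRI on the same formula with SD 1.5: power 0.80-0.83 at 20/20% dropout, and a difference of 0.35-0.49 cm² at 30/10%.

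**3. Reading B, imputation from baseline variables (VAS).** Simulation: 100 per arm, 800 replicates, 10 imputations by arm, ANCOVA on baseline. Assumptions: between-visit correlation 0.4 + 0.6 × 0.7^lag, placebo improvement 10 mm, and logistic dropout that is either random or depends on the last observed pain. True difference 10 mm unless stated.

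| Dropout mechanism | Dropout placebo/MTX | Baseline-only MI | MI with interim visits |
|---|---|---|---|
| Completely random | 20/20% | 9.9 mm, SE 2.69 | 9.9 mm, SE 2.65 |
| Pain-driven, same in both arms | 30/25% | 9.8 mm | 10.3 mm |
| Pain-driven, placebo only | 30/19% | 7.9 mm, power 0.78 | 9.8 mm, power 0.94 |
| Pain-driven, opposite directions | 30/27% | 6.0 mm, power 0.53 | 10.0 mm, power 0.92 |
| Pain-driven, placebo only, no true effect | 30/19% | −2.2 mm, rejection 0.118 | −0.2 mm, rejection 0.040 |

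In the last row the complete data gave −0.25 mm, so about 2 mm of the −2.2 mm is due to the imputation. The pain-driven mechanisms depend on observed pain, so they are MAR by construction once the interim visits are used. Most of them also exceed 20% dropout.

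**4. MRI.** Scans are scheduled only at screening and week 52, plus a withdrawal scan sought after at least 24 weeks. Baseline is therefore the main MRI information for a leaver. What reading B loses is the auxiliary pain data and any withdrawal scans.

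**The case against.** The sentence does not say that baseline data are the only source. Withdrawal scans and pain levels are sought, and nothing says they are discarded. A condensed article may leave the covariates of an imputation model to the SAP, and the reference to MAR fits model-based imputation better than carrying baseline forward. This stands in part: a reader might infer that post-baseline data are excluded by rule, and the text does not go that far. But it does state a source and an assumption, it names nothing else, and no other section repairs it. The point is about a stated rule, not about silence.

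The larger figures are also conditional. The 12% type I error needs reading A, a 30/10% split and a 10 mm improvement in both arms. It falls to about 7% at 25/15% and to the nominal 5% if neither arm changes. The 20% is an allowance, not a forecast, and the documents predict no difference in dropout between arms. The Safety assessments section calls the drug well tolerated by most patients, stopping study drug is not the same as losing outcome data, and unblinded participants stay in follow-up. All of this stands. It limits the size of the problem but does not make the sentence workable.

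**Conclusion.** The concern holds in a conditional form. Reading A contradicts MAR. With equal 20% dropout it shrinks both planned differences by a fifth while VAS power stays at about 84-88%. With unequal dropout it can bias the estimate in either direction. Reading B leaves out four scheduled visits of pain data. It is nearly harmless when dropout is random or driven alike in both arms, but took a true 10 mm to 7.9 or 6.0 mm when pain-driven dropout differed by arm.

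A reader might infer that either reading necessarily gives a biased result, or that a 12% error rate is to be expected. The documents support neither, because the unequal dropout, the placebo improvement, the correlations and the dropout mechanisms are all assumed. Nor does the argument about interim visits reach both co-primaries equally: it applies to VAS and WOMAC, and only weakly to MRI. The sample size is unaffected. The sentence should still be replaced, since the dropout mechanism cannot be known in advance and the better method uses data already collected.

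**What to change.** Replace the imputation sentence, before unblinding, with the following.
- **VAS and WOMAC:** a likelihood-based repeated-measures mixed model on all post-baseline visits (weeks 4 to 52) with baseline, treatment-by-visit and site, and the week-52 contrast as primary. Multiple imputation that includes the interim visits is an acceptable alternative.
- **MRI volume:** multiple imputation by arm using baseline volume, site, the pain visits and any withdrawal MRI.
- **Sensitivity:** keep baseline carried forward only as a sensitivity analysis, labelled as such. A delta-adjusted analysis is optional.

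Cost: a change of wording and modest programming. No new data are needed and N = 200 stands.

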### Withdrawal

All participants are able to withdraw at any time of the trial. The time and reason will be recorded. If participants withdraw after 6 months of follow-up, we will attempt to obtain their final MRI scans and pain levels.

### Oversight and monitoring

The chief investigator, project manager, enrolling research staff, and three independent Clinical Research Associates from the Clinical Research Centre of Zhujiang Hospital comprise the Operation Committee (OC) at the coordinating centre. The OC will have weekly meeting and audit trial conduction in each institution for at least three times a year. Patient recruitment and data quality will also be checked regularly. The PIs, the consultants, and the biostatistician comprise the Trial Steering Committee (TSC), which provides supervision of trial development and oversees trial progress. The frequency of TSC meetings will be determined by PIs and the funder. There is no specific stakeholder and public involvement group in the current study. The Data Monitoring Committee (DMC) consists of a statistician, two research doctors, the CI, and an independent chair without any competing interests. The DMC will oversee data integrity, security, and efficacy; guide blinded primary data analyses; and report study results.

